## Abstract

**Background:**

Chronic medical illnesses significantly and negatively affect the quality of life of individuals who suffer them and represent one of the most important challenges faced by healthcare providers and policy-makers due to its rising prevalence and high rates of comorbidity. Compassion-based interventions delivered over the Internet may be a useful approach to facilitate illness management and improve the quality of life of individuals with chronic medical conditions.

**Objectives:**

The purpose of this study is to describe a protocol for a randomized controlled trial to test the efficacy of the Internet Attachment-Based Compassion Therapy (iABCT) to improve the quality of life and well-being of patients with chronic medical illnesses.

**Method:**

A two-arm, parallel-group, randomized controlled trial (RCT) will be carried out, with three assessment points (baseline, 3-month, and 6-month) under two conditions: intervention group and control group (waiting list). The primary outcomes include the quality of life on the EuroQol 5-Dimensions Questionnaire (EQ-5D) and the Pemberton Happiness Index (PHI). Secondary outcomes, such as compassion, self-care behaviors, illness interference, self-criticism, symptomatology, attachment styles, social support, and illness perception, will be considered. Moreover, an assessment on satisfaction and usability will be carried out. A total of 68 participants as minimum will be recruited (34 per arm). Intent-to-treat mixed-model analyses without any ad hoc imputations will be conducted.

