#### Primary outcome measure

*Quality of life*. The EuroQol 5-Dimensions Questionnaire (EQ-5D; [43]) is a self-report measure that assesses the health-related quality of life (HRQOL) using five dimensions of functionality in daily-life: mobility, self-care, usual activities, pain/discomfort and anxiety/depression. and three levels of severity. Responses in each dimension are divided into three levels of severity: (1) no problems; (2) moderate problems; and (3) extreme problems. Moreover, the EQ-5D includes a visual analogue scale (EQ VAS) in which participants self-rate their quality of life in a range from 0 (worst imaginable health state) to 100 (best imaginable health state). The Spanish version of this scale has shown good reliability and validity properties [44].

*Well-being*. The Pemberton Happiness Index (PHI; [45]) is a scale which includes 11 items related to different domains of remembered well-being (general, hedonic, eudaimonic, and social well-being) and ten items related to experienced well-being (i.e., positive and negative emotional events that possibly happened the day before); the sum of these items produces a combined well-being index that ranges from 0 to 10. Results from the Spanish validation study provided very good support for the psychometric properties of the PHI (α = .92) ([45]).

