### Sample size

The sample will be composed of 68 participants as minimum. The sample size was calculated using the G*Power 3.1.9.7 for Windows program [68]. Estimated sample size was decided based on medium effect sizes (d = 0.4), statistical power of .80 and α = .05, indicating a necessary sample of 52 participants [69]. Considering that the dropout rate in Internet-based interventions for the chronic medical ill population is usually around 30%, a target of 34 people per group was set [70–72].

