### Statistical methods

The latest version of SPSS (v.26) will be used for all data analysis. T-tests for independent-samples (t), ANOVAs, and chi-square analysis (χ2) will be calculated to investigate the characteristics of the randomized sampled and included in the RCT and to explore group differences in participants’ sociodemographic (e.g., age, gender) and clinical data (e.g., quality of life, well-being). Attrition and dropout rates will be calculated by reporting percentages and patterns of missing data. Intent-to-treat mixed-model analyses without any ad hoc imputations will be used to handle missing data in case of participant dropout and to conduct the efficacy analysis [73]. This analysis compares the study groups based on the treatment to which they were randomly allocated. It does not assume that the last measurement is stable, it does not involve any substitution of missing values with supposed or estimated values, it is conducted using all available observations, thus reducing the biases and loss of power caused by the simple deletion or random imputation of incomplete data. Mixed-model analyses are appropriate for RCTs with multiple time points and pre-post designs, and it has showed remarkable robustness to violations of distributional assumptions (e.g., skewed, kurtosis, or heteroscedastic) [74, 75]. To study distributional assumptions and the impact of missing random effect components on model some test will be included: Normality assumptions will be explored using the Shapiro-Wilk test (for each experimental group, N < 50), the Kolmogorov-Smirnov (K-S) test (for the total sample, N > 50), skewness and kurtosis indices, and normality plots (Q-Q plots). Homoscedasticity will be explored by Levene’s test and Box’s M test for equivalence of covariance matrices. Wald statistic (or Z-test) will be conducted to test the residual error variance estimation and the null hypothesis of homogeneity of residuals. The assumption that data is missing completely at random (MCAR) will be evaluated using Little’s MCAR test. it is robust to violations of distributional assumptions. A linear mixed-effect model for each outcome measure will be implemented using the MIXED procedure with one random intercept per subject. An identity covariance structure will be specified to model the covariance structure of the intercept. For each outcome, time (baseline and 3- and 6-month follow-up) will be treated as a within-group factor and group (experimental and control group) as a between-group factor and significance effects will be followed up with pairwise comparisons (adjusted by Bonferroni correction). Cohen’s d effect size and 95% CI will be calculated for within- and between-group comparisons [76, 77]. Sensitivity analyses will be performed to assess the robustness of the findings in terms of different methods for handling missing data (i.e., mixed models with and without imputation, maximum-likelihood estimation, and maximum-likelihood multiple imputation [78]. The means and standard deviations of the acceptability measures of the intervention will be analyzed. For analyses of associations between intervention outcomes, predictors of change and mechanisms of action, several statistical tests such as Pearson’s correlation, multiple regressions and mediation analysis will be performed. In addition, participants’ qualitative responses regarding facilitators and barriers to the intervention will be explored using a qualitative content analysis and coding and categorization approach to the data using word frequency counts with ATLAS.ti software.

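### Two primary outcomes have no error control across them and the EQ-5D score is not named; if either outcome can carry the claim, the two-sided false-rejection rate is about 8–10%, or 10–14% with three scores

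*Protocol article*

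**What the plan says.** The abstract (Method) states: "The primary outcomes include the quality of life on the EuroQol 5-Dimensions Questionnaire (EQ-5D) and the Pemberton Happiness Index (PHI"). The section Primary outcome measure lists the same two instruments.

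That section treats the two differently. For the PHI it names one score: "the sum of these items produces a combined well-being index that ranges from 0 to 10". The EQ-5D is described as a profile, "using five dimensions of functionality in daily-life: mobility, self-care, usual activities, pain/discomfort and anxiety/depression", with three severity levels per dimension, followed by a second measure: "Moreover, the EQ-5D includes a visual analogue scale (EQ VAS) in which participants self-rate their quality of life". No summary index or value set is mentioned, and neither the profile nor the VAS is called the primary score.

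Statistical methods assigns a separate linear mixed model to every outcome, with time and group as factors. On multiplicity it says only that "significance effects will be followed up with pairwise comparisons (adjusted by Bonferroni correction"). It closes by saying that analytic methodology will be reviewed before the data are analysed.

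Alpha appears once, under Sample size: "medium effect sizes (d = 0.4), statistical power of .80 and α = .05, indicating a necessary sample of 52 participants". It is not divided between the primaries. Hypothesis (a) under Objectives sets the efficacy comparison at 3 months and lists quality of life, well-being and the secondary variables together, with no rule for what counts as success.

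**The concern.** The stated Bonferroni rule works inside one outcome's model, after an effect there is significant. It does nothing about having two primary outcomes, each with its own chance of a false rejection. No hierarchy, alpha split or joint-success rule fills the gap.

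The EQ-5D adds a second problem. Five three-level items cannot be the single response in a linear mixed model, so the analyst must choose a score that the article does not name: an index, the VAS, or both. If that choice is made after results are seen, the number of primary tests is no longer fixed. At stake is whether a headline claim about quality of life and well-being carries the 5% error that a reader would assume.

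**Working it through.** **Inputs from the article.** Two primary instruments (abstract; Primary outcome measure). One model per outcome and Bonferroni within an outcome (Statistical methods). Alpha .05, power .80, d = 0.4 and N = 52 (Sample size).

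**Assumptions.** Tests are two-sided; each primary is tested at .05; one significant primary is enough for the claim; the test statistics have a common correlation r. The article gives no value for r, so a range is shown.

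**1. The plan's own figure.** N = 52 is reproduced by a repeated-measures group-by-time interaction with f = d/2 = 0.2, two groups, two measurements and an assumed within-person correlation of 0.5. The noncentrality is 0.2² × 52 × 2 / (1 − 0.5) = 8.32 on 1 and 50 degrees of freedom, giving power 80.7% at alpha .05. A two-sided paired t-test with d = 0.4 also gives 52. The article does not say which method was used. In either case the figure covers one test at .05.

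**2. Chance of at least one false rejection.** For k independent tests this is 1 − 0.95^k:
- k = 2: 1 − 0.95² = 9.75%
- k = 3: 1 − 0.95³ = 14.3%

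For correlated tests, 2 million equicorrelated normal draws with cut-off ±1.96 gave:

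| r | Two scores (one EQ-5D score, PHI) | Three scores (index, VAS, PHI) |
|---|---|---|
| 0 | 9.75% | 14.3% |
| 0.5 | 9.0% | 12.5% |
| 0.7 | 8.4% | 10.9% |
| 0.8 | 7.8% | 9.9% |

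**3. False rejections in favour of iABCT only.** Each test has a 2.5% chance. If independent: 1 − 0.975² = 4.9% and 1 − 0.975³ = 7.3%. At r = 0.8 the simulation gives 3.9% and 4.9%.

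**4. After correction.** With two tests at .025 each, 1 − 0.975² = 4.94% two-sided if independent. If both outcomes must succeed at .05, the chance that both are falsely rejected cannot exceed 5%.

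**5. Cost in power.** On the method of step 1, with N = 52, testing at .025 gives 71.6% instead of 80.7%. As a check, take a two-sample t-test with 26 per arm and the effect that gives about 80% at .05 (d about 0.79, chosen only for this calibration and not in the article): power at .025 is 70%. The normal approximation agrees: 1.960 + 0.842 − 2.241 = 0.561, and Φ(0.561) = 71%.

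**The case against.** The strongest reply is that this is a journal article. A statistical analysis plan that is not shown could name the EQ-5D score and set a rule across the primaries, and nothing in the article rules that out. That limits the point but does not remove it. The article does choose a multiplicity rule, and the rule it chooses misses the primary family. It also states a single score for the PHI but none for the EQ-5D, in the same section.

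A second reply is that the aim is worded jointly, as quality of life and well-being, so both might be meant to succeed. Error would then be at most 5% with no adjustment. The article does not say this, and hypothesis (a) attaches all the secondary variables to the same sentence, so it cannot sensibly be read as requiring every listed outcome. Nor does it say that one outcome is enough; that remains an assumption of the figures. The 5% level per outcome is likewise inferred, from the single alpha, the separate models and the absence of a cross-outcome correction.

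A reader might infer two stronger things that the article does not support:
- **That 8–14% is the chance of a false claim of benefit.** It is the two-sided rate, which includes false findings against iABCT. The rate of false claims of benefit is about half.
- **That there are seven primary tests (five dimensions, VAS and PHI), with error near 30%.** That needs seven independent tests, 1 − 0.95⁷ = 30.2%. No section proposes testing each dimension as a primary; the dimensions are listed to describe the questionnaire.

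Open allocation adds little to the argument. A score can be chosen after the results in a blinded trial too.

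**Conclusion.** The point stands as a gap in the stated multiplicity rule together with an undefined EQ-5D endpoint. Under the assumptions listed, two-sided error across the primaries is about 8–10% for two scores and about 10–14% for three, for r from 0.8 to 0. In the direction of benefit it is about 4–5% and 5–7%, against 2.5%. With two scores correlated above 0.8 the two-sided figure drops a little below 8% (7.0% at r = 0.9). If the sponsor intends both outcomes to succeed, there is no inflation and only that rule needs stating. In either case the EQ-5D score still has to be named. The change should be made, but the gap does not undermine the design.

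**What to change.** Before any outcome data are viewed:

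1. Name one EQ-5D score as primary. The 0–100 VAS fits the linear model as described; the index would also do if its value set is stated. Make the remaining EQ-5D scores secondary.
2. Define the primary family as the two 3-month between-group contrasts, one for that EQ-5D score and one for the PHI. The waiting-list group gains access to iABCT after the 3-month assessment, so this is the last comparison with an untreated control.
3. Either apply Holm across these two contrasts (the smaller p-value against .025 and, if that is significant, the other against .05), or state that both must be significant at .05.
4. Restate the power paragraph under the rule chosen.

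This is a change of wording, with a cost in power. Under Holm, a single outcome at the first step has about 70–72% power under a calculation that gives about 80% at .05. Bringing it back to 80% on the repeated-measures method would take 62 participants before dropout instead of 52; I would report the lower power and not enrol more. Under the joint rule alpha is unadjusted, but power for the claim falls: with 80.7% for each outcome it lies between 0.807² = 65% (independent) and 80.7% (fully correlated).

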**Conclusions:**

Findings of this study will provide new insights into the potential of self-applied compassion-based interventions (CBI) delivered online in the context of chronic medical illnesses, considering aspects of their implementation (e.g., facilitators, barriers) and mechanisms of change.

**Trial registration:**

The study is registered under Clinicaltrials.gov (NCT04809610) and it is currently in the participant recruitment phase.

## Introduction

Chronic illnesses are defined as non-communicable diseases that last one year or more, require ongoing treatment or suppose a significant functional alteration or both [1, 2]. Due to its rising prevalence along with their important consequences (e.g., hospitalization, long-term disability or work limitations), these conditions are becoming a significant burden not only to individuals who suffer them, but also their families and society [3–5].

Furthermore, there are high rates of comorbidity between mental health problems and chronic medical conditions, being one of the most important challenges faced by health-care providers and policymakers [6, 7]. These comorbidities have been extensively reviewed [8, 9], and studies have shown that individuals with chronic medical illnesses (e.g., chronic pain, diabetes or inflammatory bowel disease) commonly experience depression or anxiety [10–12], and negative health outcomes such as low satisfaction with life [13] or diminished quality of life [14]. This comorbidity reflects a reciprocal interaction in which the negative consequences of the disease not only depend on the course and severity of the illness itself, but also on other psychological processes. For instance, the psychological adjustment process to the disease, the coping strategies to face stress associated with the disease, and the patient’s illness management have a direct influence on physical health, including morbidity, mortality and disease complications [15–18]. Likewise, detrimental psychological processes (e.g., illness-related shame, self-criticism or rumination) suppose a barrier to implement self-care behaviors involved in an adaptive illness management (e.g., treatment plan adherence, exercising, or dietary guidelines adherence), which, in turn, could further increase distress, worsen prognosis and detriment the quality of life [19–22]. As a consequence, both self-care behaviors included in the illness management as well as detrimental psychological processes have become a target of different psychological interventions aimed at promoting quality of life of the population with chronic medical illness [23].

This is the case of compassion-based interventions (CBI), which refer to psychological interventions aimed at enhancing compassionate and self-compassionate responses which involve the recognition of suffering and the inclination to relieve it with an act of kindness rather than criticizing, blaming, or pitying [24]. Compassion and self-compassion may be a useful approach to illness management since they involve accepting suffering as an inevitable human condition and facilitate a kinder and more compassionate attitude towards difficulties [25].

Several studies have shown that CBIs can be especially beneficial for improving the quality of life of people with chronic illness [26–28]. Two recent systematic reviews have concluded that CBIs are effective in populations with chronic medical conditions, as their results showed improvements in different physical and psychological outcomes such as depression, anxiety, self-compassion and health-related quality of life [29, 30].

In sum, being able to approach difficulties with a compassionate attitude helps individuals to feel empowered with new management strategies and promote a sense of calm and agency to provide comfort to themselves, which facilitates the implementations of self-care behaviors and adaptive illness management.

One of the CBI that has proved its efficacy on both healthy population and patients with chronic medical conditions is the Attachment-Based Compassion Therapy (ABCT) [31]. This therapy is based on attachment theory [32], which provides a framework for understanding the links between close relationships and psychopathology and includes specific practices to identify and develop a secure attachment style to promote compassion for oneself and others [33]. Specifically, the ABCT has shown its efficacy and applicability for the treatment of fibromyalgia showing improvements on psychological outcomes such as functional status [34] and biological outcomes such as reduced brain-derived neurotrophic factor (BDNF) and inflammatory biomarkers [35]. There are specific delivery barriers that could interfere with the effectiveness of CBIs in people with chronic illnesses, such as limitations of access, mobility, or transportation. In order to tackle these limitations and to respond to the growing need of healthcare systems for scalability and sustainability, evidence-based interventions can benefit from adapting its delivery format through information and communications technologies (ICTs) [36, 37]. In fact, previous research supports the notion that the psychological outcomes of people living with chronic illnesses can be improved with a self-delivered online intervention (e.g. [38, 39]) and incipient evidence shows the potential value of delivering CBIs online in the context of chronic illnesses [40, 41]. Moreover, other results show that adapting CBIs to an online format may improve adherence and facilitate the involvement of chronic patients in a better management of their illness [37]. Regarding the ABCT approach, an online version (iABCT) has been developed to be totally self-applied over the Internet for Spanish speakers. The iABCT is currently be assessed in a feasibility study for general population [42].

In conclusion, CBIs delivered through the Internet seem to be a helpful cost-effective solution, and incipient research is exploring the feasibility and acceptability of the iABCT on a Spanish general population [42]. Therefore, more research is needed on their efficacy in a context of chronic medical conditions. The present study is the first attempt to explore the efficacy of the iABCT to improve quality of life and well-being in this population.

### Objectives

The main goal of this study is to describe a randomized controlled trial (RCT) to test the efficacy of the iABCT [42] to improve the quality of life and well-being in a population with chronic medical illness, compared to waiting list (WL) as a control condition.

In particular, this study has seven specific objectives: (1) to analyze the efficacy of the iABCT program in improving quality of life and well-being and other secondary outcomes (compassion, self-compassion, self-care behaviors, illness interference, self-criticism, symptomatology, attachment styles, social support, illness perception) at 3-month follow-up after baseline compared to the WL group; (2) to provide 6-month follow-up data on the maintenance or generalization of the achievements in the intervention group; (3) to analyze the acceptability of the iABCT program in terms of expectations, satisfaction, usability and opinion by the participants; (4) to provide 6-month follow-up data for the control group after receiving the iABCT; (5) to analyze which patient profile (i.e., sociodemographic and clinical baseline variables) predicts the improvement in quality of life and well-being after receiving iABCT in the follow-up sessions; (6) to analyze which mechanism of change predicts the greatest change in measures related to quality of life and well-being in the follow-up sessions; and (7) to identify possible facilitators and barriers to the use of this type of protocols (e.g., treatment logic, duration, format, usability) taking into account the participant’s perspective through a semi-structured qualitative interview.

We hypothesize that: (a) iABCT condition will be more efficacious than the WL group in improving quality of life and well-being and other secondary variables at 3-month follow-up; (b) the gains achieved after iABCT will be maintained at 6-month follow-up; and (c) the iACBT will be well accepted in terms of expectations, satisfaction, usability and opinion by the participants; (d) participants in WL group will show an improving quality of life and well-being and other secondary variables at a 6-month follow-up, once they receive the iABCT; (e) improvements in quality of life and well-being scores will be predicted by self-reported self-compassion and secure attachment; (f) frequency of meditation practice will moderate the improvement in quality of life and well-being after receiving the iABCT; and (g) changes in compassion, self-criticism and attachment style will appear as mediators of greatest changes in quality of life and well-being. Regarding objective 7, no specific hypotheses are proposed due to the exploratory nature of the qualitative analyses.

